## Abstract

**Background:**

Regular participation in moderate-to-vigorous physical activity (MVPA) is important to manage obesity. Physical education (PE) is considered to play an important role in promoting lifelong participation in physical activity (PA) because it provides an existing network where cost-effective interventions can be implemented to produce sustainable change in health behavior. However, the association between compulsory school PA (e.g., PE lessons) and body composition levels has received mixed support in the literature. Therefore, the present study aimed to investigate whether a school-based intervention targeting salient PA benefits and barriers grounded on the theory of planned behavior would promote young people’s participation in MVPA during leisure time and reduce body mass index (BMI) of overweight students.

**Methods/design:**

A total of 171 students from 3 secondary schools in Singapore underwent the control condition followed by the intervention condition. Both the conditions consisted of PE lessons twice per week over 4 weeks. In the control condition, PE teachers encouraged students to participate in PA during leisure time without providing persuasive message. While in the intervention condition, PE teachers delivered persuasive messages that targeted the salient benefits and barriers associated with PA to the students at the last 5 to 10 min of each PE lesson. PA levels over a week were measured objectively with wrist-mounted GENEActiv Original accelerometers and subjectively with self-reporting questionnaires three times (Baseline, Post 1, and Post 2) in each condition. Student’s self-reported PA level was measured using the Leisure-Time Physical Activity Participation Questionnaire and the International Physical Activity Questionnaire, and their attitudes, intentions, subjective norms and perceived behavior control towards leisure-time PA were measured with a questionnaire based on the theory of planned behavior. Furthermore, students’ intention, determination and willingness to engage in leisure-time PA were compared with the other activity (e.g., doing homework, shopping).

**Discussion:**

This study will provide the evidence on the effectiveness of a cost-effective school-based intervention on reducing BMI of overweight students through promoting sustained participation in leisure-time PA. It will also address methodological issues on the gaps between objective and subjective measures of PA.

**Trial registration:**

This trial is registered with the ISRCTN registry (ISRCTN73786157, 26/10/2017, retrospectively registered).

## Background

Ministries and organizations worldwide have recognized that adopting moderate-to-vigorous physical activity (MVPA) is an important strategy to help manage obesity while at the same time improves mood by assisting individuals to cope with stress [1]. There is a close relationship between physical activity (PA) and productivity where individuals who engaged in regular PA experience higher levels of psychological well-being and are more productive in school or at workplace as compared to individuals who are physically inactive [2].

Physical education (PE) in schools is considered to play an important role in promoting lifelong participation in PA because it provides an existing network where cost-effective interventions can be implemented to produce sustainable change in health behavior [3–5]. In fact, one of PE goals highlighted by Singapore Ministry of Education is associated to the benefits of living a physically active and healthy life through regular participation in PA [6]. However, teachers and health professionals have found it challenging to motivate children to engage in PA via school-based interventions [7, 8]. A study [9] demonstrated that provision of compulsory school PA was not associated with participation in PA, fitness or body composition levels (e.g., body mass index [BMI]) in adulthood. Findings of systematic review and meta-analytic studies also rose questions about the value of school programs on improving BMI [10, 11].

### Theoretical framework

Interventions are likely to be successful with motivating individuals to participate in PA when they are based on rigorous theory and their content is informed by theories of human motivation [12, 13]. This is supported by a growing body of literature that shows that theory-based interventions produce more sustainable changes in leisure-time PA when compared to interventions that are not based on theory [14]. For example, intervention programs that were based on the theory of planned behavior (TPB) were found to be effective in promoting PA [15–18]. Although intervention programs based on the TPB have been conducted to university students, adults or the senior citizens, there is relative dearth of research that targeted the promotion of health behaviors in classroom settings. To fill the gaps in literature, it is useful to develop a school-based intervention program by adopting Ajzen’s TPB [19] and evaluate its effectiveness in promoting MVPA during leisure time.

Only a few studies have been conducted to test the effectiveness of the TPB in promoting PA during leisure time among young people [20, 21]. Consistent with the theory, the studies showed that the effectiveness of interventions depends on two factors: (a) information saliency and (b) the types of beliefs communicated during intervention periods. As for the first factor, school-based interventions were found to be effective when they communicated salient information that adolescents “felt” personally relevant or important to themselves [20, 21]. For example, persuasive messages that emphasized on enjoyment of leisure-time PA elicited more positive responses than those that emphasized on reducing the risk of cardiovascular diseases since adolescents perceived getting a heart attack as a remote prospect for them [20].

The second factor is related to the types of beliefs communicated during intervention periods. According to the TPB, interventions may target behavioral beliefs by emphasizing salient benefits or de-emphasize disadvantages associated with PA through attitudes (individuals’ positive vs. negative evaluations toward PA) and intentions (the extent to which individuals are willing to exert effort towards performing PA). Alternatively, interventions may target normative beliefs which emphasize the attitudes of significant others (e.g., attitudes of teachers or parents) towards PA. The interventions that target normative beliefs are likely to influence PA participation through subjective norms (individuals’ beliefs about whether significant others approve or disapprove PA participation) and intentions. Further, interventions may assist people to overcome salient barriers by targeting control beliefs. Interventions that target control beliefs are likely to affect PA participation through perceptions of their behavior control (individuals’ beliefs about whether they possess the necessary resources or skills to perform PA or overcome barriers) and intentions. The model underpinning the TPB is presented in Fig. 1. A pilot study was recently conducted to examine the effectiveness of a school-based program in promoting leisure-time PA for secondary school students [21]. The intervention program targeted on salient benefits and barriers to doing PA. To examine the duration of the intervention program, it was conducted over 8 weeks to half of the participants but only for 4 weeks to the other half of the participants. Results of the pilot study revealed that regardless of the intervention duration, the average leisure-time PA increased from the baseline to the midpoint of the intervention period (4 weeks after the baseline) and it was maintained until the end of the program (8 weeks after the baseline). Although these results were encouraging, the pilot study had several limitations. First, the usefulness and cost-effectiveness of the intervention program on reducing BMI were not evaluated. Second, the PA participation was measured only with self-reported questionnaires and the sustained leisure-time PA level was not assessed with an objective measure. Finally, there was no comparison on the effectiveness of the intervention with those who did not receive an intervention as the pilot study did not include a control group.

**Fig. 1 Fig1:**
[figure not shown]
Model of the theory of planned behavior

### Aims of the study

The present study aimed to investigate whether a school-based intervention targeting salient PA benefits and barriers grounded on the TPB would promote young people’s participation in MVPA during leisure time and reduce BMI of overweight students.

It was hypothesized that a) the proposed school-based intervention program grounded on the TPB would be useful to promote young people’s participation in MVPA during leisure time (*H*_*1*_), b) overweight student’s BMI would be reduced after the intervention, compared to their BMI in the control condition (*H*_*2*_), and c) the effects of the intervention program on PA intentions and participation as well as BMI would be medicated by students’ attitudes and perceptions of behavior control (*H*_*3*_).

## Methods/design

### Study design

The Institutional Review Board at Nanyang Technological University (Singapore) provided ethical approval for the current study. Although the study was originally planned to conduct as a cluster-randomized controlled trial, the original plan had to be changed due to great difficulty in recruiting schools. This study adopted a 2 (type of conditions: control vs. intervention targeting salient PA benefits and barriers) × 3 (measurement points: Baseline, Post 1 and Post 2) within-subjects design in which all participants underwent the control condition followed by the intervention condition. Figure 2 provides the flow of the study design.

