### Procedure

Prior to the commencement of the study in each condition, students’ body compositions (e.g., height, body mass and body fat percentage) were measured at their school. Height was measured using a ruler attached to the wall to the nearest 0.5 cm, body mass and body fat percentage were measured with a body composition monitor (Omron Karada Scan: HBF-362). Students were also asked to complete a demographics sheet and a set of self-report measures of leisure-time PA and psychological variables (Pre-Baseline). After completing the questionnaire set, students were instructed to wear the GENEActiv (Original) accelerometer (Activinsights Ltd, Cambridgeshire, UK) on their non-dominant wrist for one week to objectively measure frequency and intensity of their PA level (Baseline). When students returned the accelerometer, they were also asked to complete another set of the same self-report measures (Baseline). Subsequently, students spent four weeks in the control or intervention condition. During the 4 weeks, an intervention program was conducted in PE lessons in the intervention condition. After the 4 weeks, students were requested to wear the accelerometer again for one week across two occasions (Post 1 and Post 2) with a 4 weeks interval period in between before measuring their body compositions and completing the same set of self-report measures. Students’ height, body mass and body fat percentage were measured at three occasions (Pre-Baseline, Post 1 and Post 2) in each condition (see Fig. 2).

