### Intervention and fidelity check

PE lessons were conducted twice a week over 4 weeks in both control and intervention conditions. In the control condition, PE teachers encouraged students to participate in PA during leisure time without delivering persuasive messages in PE lessons. An intervention program was implemented after the control period was over (see Fig. 2).

Prior to the intervention period, PE teachers were trained on how to deliver persuasive messages through a 3-h workshop. During the workshop, PE teachers were encouraged to express their concerns about delivering persuasive messages, researchers addressed those concerns to assist PE teachers to conduct the intervention at a sufficient level of proficiency. The persuasive messages targeted salient information related to the benefits and barriers associated with PA, which were identified based on the results of surveys conducted for students at Pre-Baseline in the control condition. Some examples of salient benefits were “health benefits”, “improving physical skills and fitness”, “fun and socialization” and “recommended physical activity level”, whereas salient barriers were “lack of time”, “lack of facilities or equipment”, “feeling tired” and “weather”.

In the intervention condition, PE teachers delivered the persuasive messages that targeted the salient benefits and barriers associated with PA at the last 5 to 10 min of each PE lesson. After PE teachers delivered the persuasive message, students were asked to answer a question about the message in each lesson (e.g., “Please explain briefly how do you know that MVPA improves your fitness levels?”). Researchers evaluated PE teachers’ fidelity of the interventions with a checklist (e.g., “The PE teacher provided clear instructions on this session’s message”) on a scale ranging from 1 (*not at all*) to 5 (*very much*).

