### Data analysis

To examine the first research hypothesis (*H*_*1*_), a 2 (type of conditions: control vs. intervention) × 3 (measurement points: Baseline, Post 1 and Post 2) repeated ANOVA will be conducted on students’ MVPA levels. The second hypothesis (*H*_*2*_) will be examined through a 2 (type of conditions: control vs. intervention) × 3 (measurement points: Pre-Baseline, Post 1 and Post 2) repeated ANOVA on students’ BMI levels. A path analysis will be conducted to examine the third hypothesis (*H*_*3*_) with *M*plus (Version 8) [27]. Student’s age, gender, socio-economic status, and prioritization of PA together with fidelity of intervention programs will be included as covariates in the analyses. Furthermore, correlation analyses will be conducted to examine the relationships between the subjective and objective measures of PA.

A cost effectiveness analysis of the program will also be conducted by focusing on the incremental cost-effectiveness of the intervention condition compared to the control condition. Incremental cost-effectiveness ratios will be calculated in terms of the incremental cost per unit BMI reduction. Differences in BMI between different measurement points (Pre-Baseline, Post 1 and Post 2) will also be calculated. Height will be added as a covariate in the analyses in order to account for the growth change in height over the data collection period. Incremental cost-effectiveness ratios will be calculated using standard techniques coupled with bootstrapping methodology and acceptability curves [28]. Through these analyses, it will provide information about the probability that an intervention is cost-effective.

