## Discussion

Regular participation in MVPA is well recognized as an important strategy to help manage obesity [1]. PE is considered to play an important role in promoting lifelong PA participation because it provides an existing network where cost-effective interventions can be implemented to produce sustainable change in health behavior [3–6]. However, the relationship between compulsory school PA (e.g., PE lessons) and body composition levels has received mixed support in the literature [9–11]. A growing body of literature shows that theory-based interventions produce more sustainable changes in leisure-time PA when compared to interventions that are not based on theory [14]. Intervention programs based on the TPB were found to be effective in promoting PA [15–18]. However, only a few studies have been conducted to test the effectiveness of the TPB in promoting PA during leisure time among young people [20, 21]. To fill the gaps in literature, this study was conducted to develop cost-effective novel procedures according to the previous TPB-based intervention studies and investigate the effectiveness of a school-based intervention that targeted salient PA benefits and barriers on promoting secondary students’ leisure-time MVPA as well as reducing BMI of overweight students.

The current study will make a unique contribution to literature by addressing the following research issues. First, it will provide a rigorous test of the effects of a PA intervention on BMI because reductions of BMI are more likely to be observed when individuals engage in MVPA over a prolonged period of time. Establishing a link between school-based intervention programs and BMI is an important finding because the association received mixed support in previous studies [10, 11]. The cost-effectiveness analysis in the current project is also novel because previous studies have not compared the effectiveness of TPB-based school interventions against costs [20, 21].

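### Control always precedes intervention, so only the condition × measurement-point contrast can support H1 and H2; the plan does not name it as the test or state its equal-drift assumption

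*Protocol article*

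**What the plan says.** The Study design section reports that a cluster-randomised trial was intended, but "the original plan had to be changed due to great difficulty in recruiting schools". What was run is a "within-subjects design in which all participants underwent the control condition followed by the intervention condition". The section on intervention and fidelity confirms the order: "An intervention program was implemented after the control period was over". No concurrent untreated group and no reversed order is described.

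For H1, a "2 (type of conditions: control vs. intervention) × 3 (measurement points: Baseline, Post 1 and Post 2) repeated ANOVA will be conducted" on MVPA. H2 gets the same model on BMI, with Pre-Baseline in place of Baseline. H2 itself (Aims of the study) is that "overweight student’s BMI would be reduced after the intervention, compared to their BMI in the control condition". The covariates are age, gender, socio-economic status, prioritisation of PA and fidelity. Height is added for growth, in the paragraph on cost-effectiveness. That paragraph also plans an incremental cost per unit of BMI reduction.

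On what the study will show, the Discussion says "it will provide a rigorous test of the effects of a PA intervention on BMI", and the abstract says "This study will provide the evidence on the effectiveness of a cost-effective school-based intervention".

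**The concern.** With one order for everyone, anything that changes between the first and second period changes together with condition. Examples are students growing older and heavier, season, the school calendar, and growing familiarity with the questionnaires and the accelerometer. A 2 × 3 within-student ANOVA yields three effects: condition, measurement point, and their interaction. They differ greatly in how far they are exposed to this, and the article does not tie H1 or H2 to any of them. H2 is phrased as BMI after the intervention against BMI in the control condition, which is the most exposed comparison.

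If the condition main effect is read as effectiveness, drift can pass for an effect on MVPA, or growth can hide an effect on BMI. The cost per unit of BMI reduction would inherit the same error. The Discussion and abstract state their conclusions without mentioning the fixed order as a limit.

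**Working it through.** **1. The plan's own figure.** The sample size section states 174 participants for power .90, alpha .05, partial η² = .02, 6 groups and 6 measurement points. Take f = √(.02/.98) = .1429, noncentrality f²(N − 6)(6 − 1), and 5 and 5(N − 6) degrees of freedom. This gives N = 169, or 174 when rounded up to six equal groups; power at 174 is .911. The figure reproduces. It is powered for a single six-occasion within-student factor, so it does not show which of the three ANOVA effects is meant to decide.

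**2. Lag between matched points.** From the Procedure section: one week of Baseline wear, four weeks in the condition, then students "wear the accelerometer again for one week across two occasions (Post 1 and Post 2) with a 4 weeks interval period in between". That is 1 + 4 + 1 + 4 + 1 = 11 weeks per condition. Matched points are thus about 11 weeks apart, or more if there was a gap. The flow figure is not shown, so consecutive steps are assumed.

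**3. What each effect picks up.** Place the occasions at weeks 0, 5, 10 (control) and 11, 16, 21 (intervention).
- Steady drift of s per week: the condition main effect is 11s. The interaction compares changes of (5s, 10s) with changes of (5s, 10s), which is 0.
- True effect D at Post 1 and Post 2 only: the main effect is (0 + D + D)/3 = 2D/3. The interaction contrast is D.
- A calendar shift c that begins after the second baseline: the main effect is 2c/3 and the interaction is c. This is the same pattern as a true effect, so no contrast in this design can tell them apart.

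**4. Error rates with no intervention effect.** Simulation with N = 171, within-student correlation 0.5 (assumed), an 11-week lag and 3,000 runs:

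| Assumed disturbance | Main effect significant | Interaction significant |
|---|---|---|
| No drift | 4% | 5% |
| Drift 0.005 SD/week | 23% | 4% |
| Drift 0.01 SD/week | 70% | 5% |
| Drift 0.02 SD/week | 100% | 5% |
| Shift 0.10 SD after second baseline | 33% | 16% |
| Shift 0.14 SD | 55% | 25% |
| Shift 0.20 SD | 84% | 46% |
| Shift 0.28 SD | 99% | 77% |

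Hand check of the 70%: the main-effect contrast has variance 0.5 × 6 × (1/9) = 0.333, so its standard error is √(0.333/171) = 0.044 SD. The shift is 11 × 0.01 = 0.11 SD, about 2.5 standard errors.

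**5. BMI illustration.** The documents give no growth rate. If BMI rises 0.4 to 0.8 kg/m² per year at these ages (assumption), the main effect carries 11/52 × 0.4 = 0.085 to 11/52 × 0.8 = 0.169 kg/m². The sign is against the intervention.

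**6. Price of the better contrast.** Mean of Post 1 and Post 2 minus baseline, differenced between conditions, has variance 0.5 × 2 × (1 + 1/4 + 1/4) = 1.5 and standard error √(1.5/171) = 0.094 SD. For the same D, the ratio of signal to standard error against the main effect is (1/√1.5) ÷ ((2/3)/√0.333) = 0.71.

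**The case against.** The strongest reply is that the plan already contains what is needed. Each condition has its own baseline and the 2 × 3 model includes the interaction. Nothing says that the main effect will decide, and a condensed article may leave that choice to an analysis plan. This stands in part: a reader might infer that the authors intend to test the main effect, or that the design offers no usable contrast, and the documents support neither. It does not settle the matter, because H2 as written points to a level comparison. H2 can also be read as a difference in change, but a hypothesis open to both readings needs to be fixed when only one of them is defensible.

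The fixed order and the reason for it are openly reported, so there is no question of concealment. Age and height are covariates, so growth is not ignored. They address it only in part, however, and they do nothing for season, school calendar or repeated measurement.

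A reader might infer from the BMI figures that growth would manufacture a benefit. It would not: the illustrated bias runs against the intervention. False effectiveness is the risk where drift is favourable, as it could be for MVPA, and the documents give no size for that.

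The Discussion links its rigour on BMI to prolonged activity, and on MVPA to accelerometers and fidelity checks; it does not claim rigour from allocation. That is fair, but none of these features addresses period. The study also faults its pilot for lacking a comparison with people who received no intervention, and its own comparison is with an earlier period in the same students.

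**Conclusion.** The point holds as one about which contrast may be interpreted and how the result is described. The condition main effect, and any reading of H2 as a comparison of levels, cannot be separated from period, and the main effect shrinks an effect at the two later points to two thirds. The interaction is sound under equal drift and unsound under period-specific shifts: in the simulation about 5% false positives against 16% to 77%. Those rates rest on assumed drift sizes, a correlation of 0.5, and shifts placed after the second baseline, so they show how the tests behave and do not estimate what happened in these schools. The 0.08 to 0.17 kg/m² for BMI is likewise only an illustration, under an assumed growth rate and an 11-week lag.

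The change should be made because it alters what the trial may conclude. The fixed order does not make the study worthless: it leaves a non-randomised comparison that depends on one strong assumption, which the text shown does not state.

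**What to change.** 1. In Data analysis, state that H1 and H2 are decided only by the condition × measurement-point contrast: change from own baseline (Pre-Baseline for BMI) to Post 1 and Post 2 under intervention, minus the same change under control. State that the condition main effect is not interpreted as effectiveness.
2. Reword H2 as that difference in change in overweight students.
3. Use the same difference in change as the BMI term in the cost-effectiveness ratio.
4. Qualify the effectiveness statements in the abstract and Discussion: this is a non-randomised, fixed-order comparison that assumes equal drift in both periods and cannot separate the intervention from a shift specific to the second period.

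An indicator for exam or holiday weeks is not recommended. With three schools and one order it is likely to be nearly collinear with occasion, and it could not separate period from intervention.

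The cost is wording and weaker claims, with no new data. The contrast is also less precise than the main effect (ratio of signal to standard error 0.71 under the assumed equal correlation), and the stated sample size was not calculated for it.
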